### Secondary outcome measures

*The Satisfaction with Life Scale (SWLS)* measures quality of life and well-being [53]. The five items are answered on a 7-point Likert-type scale, it ranges between 5 and 35, and higher scores indicate higher satisfaction with life. A summed score will be used in this study. The scale has shown good convergent validity, good internal consistency and test-retest correlation (*α* = .87 and *r* = .82 respectively) and a single factor solution replicated through factor analysis [53, 54].

*The Ways of coping questionnaire (WCQ)* is a self-report questionnaire designed to assess and identify thoughts and actions individuals use to cope with a stressful event [55]. A version with five of the eight subscales was used in this study; confrontive coping, self-controlling, seeking social support, escape-avoidance, and planful problem solving. It consists of 33 items rated on a 4-point Likert scale (0–3) and each subscale will be summed for a raw sum score. Higher scores indicate higher use of the coping method. According to the manual the internal consistency is acceptable (α .61–.79).

*The communication subscale from the Evaluation and Nurturing Relationship Issues, Communication and Happiness (ENRICH)* assesses feelings and attitudes towards communication in the relationship [56]. It consists of 10 items responded to on a 5-point Likert scale (range 10–50) and the summed score will be used in this study. Higher scores indicate more positive feelings and attitudes toward the partner. Discriminative and concurrent validity has been established [57]. The subscale showed good test-retest and internal consistency in a Swedish sample (.77 and .89 respectively) [56].

*The Revised Dyadic Adjustment Scale (RDAS)* assesses relationship quality [58]. The RDAS consists of 14 items designed to measure adjustment in dyadic relationships on three subscales: Consensus, Satisfaction, and Cohesion. Higher scores indicate higher consensus, satisfaction and cohesion. A total summed score will be used in this study ranging between 0 and 69. In past research, the RDAS has demonstrated support for construct validity, good internal consistency (.80 to .85 and .90) respectively for the subscales and the total score as well as good split-half reliability [58]. Cronbach’s alphas from three university clinics were .86, .87, and .89 while the test–retest correlation was .82 [59].

*The Postpartum Bonding Questionnaire (PBQ)* is a screening instrument for mother–infant bonding disorders and it is designed to provide an early indication of disorders within mother-infant bonding, a high score indicates more pathological responses [60]. The four sub-scales (Impaired bonding, Rejection and Anger, Anxiety about care and Risk of abuse) each provide a summed score from the responses on the six-point Likert-scale (0 to 5) and the total score ranges from 0 to 125. This study will report subscales and total score. The four sub-scales showed moderate sensitivity (1.0, 0.89, 0.56 and 0.28, respectively) compared to the Birmingham Interview for Maternal Mental Health and high specificity (0.85, 1.0, 0.96 and 1.0, respectively) for mother–infant bonding disorders. Test–retest reliability was .95, .95, .93 and .77 for the four sub-scales [60, 61].

*EuroQol 5D (EQ-5D)* instrument will be used to estimate the quality adjusted life years (QALYs). It is one of the most widely used health utility measures [62]. The EQ-5D is a generic instrument of health-related quality of life. It records self-reported problems in each of the five domains: mobility, self-care, usual activities, pain/discomfort and anxiety/depression. Each domain is scored/rated based on three levels of severity corresponding to no problems, some problems, and extreme problems. This enables one to obtain a population-based preference score or societal index (SI). The EQ5D-3 L tool also has a visual analogue scale (VAS) that asks participants to rate their current health from 0 (worst imaginable health) to 100 (best imaginable health) [63]. Both the index scores and the VAS score correlated highly with measures of quality of life, anxiety and depression as well as responsive to change in patients with anxiety disorders [64]. Swedish norms are available for the five domains and the VAS scale, by gender, and different age groups, as well as for the population [65].

*Short Form Health Survey – 36 (SF-36)* is a self-administered, short-form health survey with 36 questions. It yields an 8-scale profile of functional health and well-being scores. The SF-36 is composed by eight subscales, each of which range from 0 to 100. A high score indicates better health (range 0–100) [66]. A total score of 50 corresponds to the mean of the general population with a standard deviation of 10. The SF-36 has demonstrated good internal consistency and factorial validity [67]. It will be used to capture the HRQoL of the study participants. This will be used in the health economic evaluation analysis (cost utility analysis). The SF-36 tool was chosen because it is sensitive and relatively well correlated with mental health disease specific tools e.g. DASS-21 for Depression [68].

### Outcomes for the partner

The partner answers WCQ, PBQ, SWLS, R-DAS, the communication subscale from ENRICH, EQ5D, and the SF-36 (see above). In addition, the Hospital Anxiety and Depression Scale (HADS) [69] is used to assess symptoms of anxiety and depression among the partners. It was developed to assess anxiety and depression symptoms among somatic care seeking patients during the previous week. There are seven items each for anxiety and depression. The responses are rated on a 4-point Likert scale and the scores are summed within depression and anxiety. The scores range between 0 and 3 for both depression and anxiety resulting in a range of 0 to 21 for each scale. Higher scores indicate more symptoms. In a review of 747 papers it was concluded that the HADS shows good validity and reliability scores [70]. Studies have reported good validity and reliability, with good internal consistency for anxiety (α = .84) and depression (α = .82) as well as for the full scale (α = .90) among Swedish respondents [71].

### Swedish national registers

#### The medical birth register

Information from the prenatal care; data on the mother, smoking and use of oral tobacco, cohabitation status, information on previous pregnancies, maternal medical drug use during pregnancy, diagnoses before and during pregnancy. Information from the delivery care; maternal diagnoses, mode of delivery, foetal presentation, analgesia and anaesthesia and hospital code. Information from the neonatal care: the infants birth weight, body length and head circumference, single or multiple birth, duration of pregnancy, Apgar score, infant diagnoses, live birth and/or stillbirth.

#### The National Patient Register

Patient data; personal registration number, gender, age, place of residence. Geographical data; county, hospital/clinic, department. Administrative data on in- and outpatients; Date of admission and discharge, length of stay, unplanned/planned admission, admitted from and discharged to. Acute care data; type of department, date and time point (admission, assessment by physician, discharge, terminated visit). Compulsory admission and detention under the Swedish Mental Health Act and Forensic Psychiatric Care. Medical data; main and secondary diagnosis, external cause of injury and poisoning, and procedures.

#### The Swedish prescribed drug register

Dispensed item (e.g. substance, brand name, dosage, amount), prescription (e.g. date of the prescription, and the date when the goods are taken out), costs (county cost and customs fee) characteristics of the workplace where the prescription was made and the profession of the prescribers.

### Health economic evaluation

A health economic evaluation in the form of a cost utility analysis will be conducted. It will focus on assessing whether iCBT + TAU is good value for the money spent compared to TAU in the management of PTSD FC and depression symptoms. The analysis will take a societal perspective as recommended by the resource allocation agencies in Sweden. The cost utility evaluation will be conducted alongside the JUNO-trial and thus intervention costs will be derived/collected from the trial data. The resource use data will be mainly collected from registers (see above), as the most important parameters here are healthcare usage and productivity losses by the mothers. The outcome measure for the study will be Health-related Quality of Life (HRQoL) captured using the EQ5D-3 L tool/SF-36 and translated into utilities. Uncertainty in the work will be addressed through sensitivity analysis and the work will be presented to a subgroup analysis level.

Reason for drop out (for mothers and their partner) will be investigated 1 year after informed consent was returned; The following open-ended question will be addressed to those who were randomized to the iCBT condition but dropped out and to those who consented to participate but did not log in to the UCARE portal; “Some time ago you were invited to, and consented to participate in, the JUNO study. What was the reason for you to not participate?”

### Statistical analysis

Data will be imported from the U-CARE web portal. For demographic data, χ^2^ and t-test will be used to examine differences between the groups at baseline. For the continuous data, a mixed model repeated measure (MMRM) will be used to evaluate treatment effects. All available data from all participants are used so this will be a suitable approach for intent-to-treat analysis. Effect sizes (Cohen’s *d*) will be based on suggestions for repeated measures and multi-level designs [72, 73] and effect sizes for planned contrasts for interactions [74]. For the binary outcome data *χ*^2^ analysis and calculations of odds-ratios will be performed. Per-protocol (defined as a minimum of four completed weeks out of six in step-1 and a minimum of six completed weeks out of eight in Step-2), completer, and drop-out analysis will be performed. Exploratory sub-group analyses will be performed between those with negative birth experience, immediate caesarean section and those with a major postpartum haemorrhage. We will also investigate differences between primiparas and multiparas, those with/without vacuum extraction, those with/ without partner involvement, as well as those with/without pro-longed labour. We will also consider known risk factors for PTSD FC as covariates.

During the study period, data from all mothers giving birth at the four trial sites will be collected from their patient records. In order to describe and compare our sample with this population we will collect a) obstetric data, b) an additional rating of overall childbirth experience and c) EPDS. The additional rating of overall childbirth experience and the EPDS is assessed at the first visit to maternal care after the birth (approximately 6–8 weeks). Subgroup investigations will be performed among those who; declined participation but were eligible, did not respond to the invitation but were eligible, were eligible but not invited (missed) and all who rated overall childbirth experience. Finally, we will report reasons for not participating among those who consented but did not participate. Statistical analyses will be performed by SPSS (IBM SPSS Statistics).

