### Sample size and power

There was a lack of studies for power calculation regarding iCBT for this population at the planning stage of this study. We therefore used information from a study that investigated iCBT for PTSD (due to other events) in a Swedish context [45]. This study had a large effect size on the continuous primary outcome measure (*d* = 1.25) in favour of the treatment group. We estimated a conservative medium effect size (Cohen’s *d* = 0.5), *α* = .05, and a power of 0.8 based on this study. A total sample size of 130 participants is needed for between-subjects t-test contrasts. For categorical outcome measures, a medium effect size (*ω* = 0.3), *α* = .05, df = 1, and a power of 0.8 was used to calculate the needed sample size. A total sample size of 88 participants is needed for *χ*^2^ analysis.

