Before discharge from hospital, women rate their overall childbirth experience on a paper and pencil administered Likert-scale (range; 0–10), please see Figure 2. Those with a low rating on the childbirth experience, defined as ≤5 on the Likert scale, and/or exposure to an immediate caesarean section and/or a major bleeding (≥2000 ml) following childbirth (see material section) are asked to consider participation in the study. Immediate caesarean section, is defined as when used for life-threatening situations for either the baby or the mother. About 8 weeks postpartum the women are contacted and informed about the study via telephone. To those interested in participation, information and consent is sent home by mail and to those not responding to contact after three attempts. Partners are also invited to participate at the same time as the mother and they sign the same consent form after reading the information about the study. Participants who consent are provided with login details to the Internet study site. The login and reporting procedures are as follows: Each login requires double authentication. At the first login, participants respond to baseline measures after which they are randomly allocated to either TAU or iCBT+TAU. They are immediately informed about the allocation via an email from the web portal. The partners are allocated together with the mothers. iCBT-1 + TAU and TAU are initiated immediately after randomisation. Participants respond to the questionnaires after iCBT step-1 (at 6 weeks) and after iCBT step-2 (at 14 weeks) followed by measurements annually up to 4 years post treatment. The U-CARE platform automatically sends reminders via email and text messages when measurements are not completed within 14 days. After another 7 days, participants are reminded via a telephone call. Paper copies of the questionnaires will be sent by mail to unresponsive participants. Reminders are also sent to those who delay their initiation of iCBT treatment and when participants delay the weekly treatment modules.

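### The plan for the TES and EPDS sums does not name the baseline score as an adjustment, so a gain in precision available at no cost is not secured

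*Protocol article*

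**What the plan says.** The Statistical analysis section of the protocol article gives the method for continuous outcomes in one sentence: "For the continuous data, a mixed model repeated measure (MMRM) will be used to evaluate treatment effects". It lists no model terms and does not say whether baseline is a response level or a covariate. The sentence on Cohen's d ends by referring to "effect sizes for planned contrasts for interactions". On covariates the section says "We will also consider known risk factors for PTSD FC as covariates"; the baseline TES or EPDS score is not named.

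The Primary outcome measures section describes the comparison differently. The mean TES symptom sum is to be compared between arms, and the between-arm difference in EPDS means is to be reported at every assessment.

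Baseline scores precede allocation. The Procedure section states: "At the first login, participants respond to baseline measures after which they are randomly allocated to either TAU or iCBT+TAU". Table 3 shows TES and EPDS at baseline and at six later time points.

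The sample size section assumes d = 0.5, alpha .05 and power 0.8, and concludes: "A total sample size of 130 participants is needed for between-subjects t-test contrasts".

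**The concern.** Two descriptions of the treatment contrast can be taken from the article, and neither brings in the baseline score as an adjustment.

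- **Interaction reading.** If baseline is one of the time points and the arms' baseline means are left free, a group-by-time contrast compares change from baseline between arms.
- **Means reading.** The arms are compared at each visit with no baseline term. This is also the contrast behind the 130.

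Both leave usable information aside. A baseline-adjusted contrast is more precise than either for any rho strictly between 0 and 1. At stake are the width of the confidence intervals for the two primary scores and the power that 130 women provide. The unadjusted calculation gives only 0.808, so there is little margin.

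**Working it through.** **Inputs from the article:** d = 0.5, alpha .05, power 0.8, total 130 (Sample size and power); 1:1 allocation (Randomisation), hence 65 per arm.

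**Assumptions, not in the article:** a two-sided test; d in units of the post-score SD; equal SDs at baseline and follow-up; complete data; baseline-to-visit correlation rho, shown over a range.

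**Step 1: reproduce the plan's figure.** An exact two-sample t-test with these inputs needs 64 per arm, 128 in total, against the stated 130. At 65 per arm the noncentrality is 0.5 × √(65/2) = 2.850 on 128 df, and power is 0.808. The stated size reproduces. A one-sided test would need only 102, so two-sided is the reading that fits.

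**Step 2: variance of each contrast, relative to the post-score variance.**

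- Unadjusted difference at one visit: 1
- Change from baseline (unconstrained interaction): 1 + 1 − 2·rho = 2(1 − rho)
- Baseline-adjusted, or arms constrained to one baseline mean: 1 − rho²

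The ratio of change to adjusted is 2(1 − rho)/(1 − rho²) = 2/(1 + rho), which exceeds 1 for every rho below 1. The change contrast beats the unadjusted difference only when 2(1 − rho) < 1, that is, when rho > 0.5.

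A generalised least squares check with seven visits, complete data and equal correlation between visits returned the same factors: 1.4 and 0.91 at rho 0.3, 1.0 and 0.75 at 0.5, 0.6 and 0.51 at 0.7.

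**Step 3: power at 65 per arm.** The noncentrality is 2.850/√factor. For example, at rho 0.3 it is 2.850/√1.4 = 2.41 for change and 2.850/√0.91 = 2.99 with adjustment.

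| rho (assumed) | Change factor | Power, change | Power, unadjusted | Adjusted factor | Power, adjusted |
|---|---|---|---|---|---|
| 0.3 | 1.40 | 0.667 | 0.808 | 0.91 | 0.843 |
| 0.4 | 1.20 | 0.733 | 0.808 | 0.84 | 0.870 |
| 0.5 | 1.00 | 0.808 | 0.808 | 0.75 | 0.904 |
| 0.6 | 0.80 | 0.885 | 0.808 | 0.64 | 0.943 |
| 0.7 | 0.60 | 0.955 | 0.808 | 0.51 | 0.977 |

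**Step 4: total number needed for 0.8 power.** Change versus adjusted: 178 and 118 at rho 0.3; 128 and 98 at 0.5; 78 and 68 at 0.7. The unadjusted difference needs 128 throughout.

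Dropout lowers power under all three. With an assumed 20% loss (52 per arm) and rho 0.5, power is 0.714 for the change contrast and for the unadjusted difference, which have the same variance there, and 0.830 with adjustment.

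**The case against.** A reader might infer that the article prescribes a group-by-time test with no baseline adjustment. It does not say so. The interaction wording stands in the sentence on effect sizes, not in the one naming the test, and it does not say that the interaction is against baseline. An MMRM can carry a baseline covariate or a common baseline mean. A condensed article commonly leaves model terms to the fuller plan, so leaving them out is not an error in itself. Maternal mental health is also among the risk factors listed in the Background, so the covariates to be considered could include baseline EPDS. All of this stands.

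A reader might also infer that the trial lacks its planned power. That needs the change contrast and a rho below about 0.5, and the article gives no rho. At 0.5 the change contrast has the planned power, and above 0.5 it has more. If d = 0.5 was meant in SDs of change, that contrast keeps 0.808 by construction. The number actually randomised is not reported either.

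What the objection does not remove is that both available descriptions omit the baseline score. The covariate sentence commits to nothing, and adjustment improves on either contrast at any positive rho below 1.

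**Conclusion.** The point holds as a free improvement. Nothing in the Statistical analysis section is shown to be wrong, and no power shortfall is established. With complete data, equal SDs and d in post-score SD units, adjustment raises power from 0.808 to 0.904 over the unadjusted difference at an assumed rho of 0.5, with a 25% cut in variance (1 − 0.75). The gain is smaller at rho 0.3 (0.843) and larger at 0.7 (0.977). Against a change contrast the gain is about 18 points at rho 0.3, 10 at 0.5 and 2 at 0.7. Adjustment is never less precise than either alternative, apart from a negligible degree-of-freedom cost.

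It would be tempting to call the change contrast biased because it over-corrects a chance imbalance at baseline. The design does not support that: the arms are randomised, so the loss is of precision.

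**What to change.** State in the Statistical analysis section that the TES sum and the EPDS sum are each analysed by an MMRM on the post-baseline visits, with fixed effects for arm, visit, arm-by-visit, the baseline value of the same score and baseline-by-visit. An alternative is to keep baseline as a response and constrain the two arms to a common baseline mean. Report the adjusted between-arm difference at each visit, derive Cohen's d from that difference, and say which SD standardises it. The same model can serve the continuous secondary scales measured at baseline.

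The cost is a sentence of plan wording and the baseline terms in the SPSS mixed model. No new data are needed, because allocation follows completion of the baseline questionnaires. The wording should be settled before outcomes are compared by arm.

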### Hypothesis

#### Primary

Women who report a negative experience from childbirth and receive iCBT+TAU will report lower levels of posttraumatic stress and depressive symptoms, as well as a smaller proportion of participants classified as fulfilling the criteria for PTSD, and a smaller proportion of participants with postpartum depression according to cut-off compared with those receiving only TAU.

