### Primary outcome measures

*The Traumatic Event Scale (TES)* measures post-traumatic stress symptoms related to childbirth, 3 months after delivery [50]. The scale was developed to assess the DSM-IV [8] criteria for PTSD FC. It comprises the stressor criterion A, with the four items formulated as follows; 1) The childbirth was a trying experience, 2) The childbirth was a threat to my physical integrity, 3) During the childbirth I was afraid that I was going to die, 4) During the childbirth I felt anxious/helpless/horrified. The response options for the A criterion are “not at all, somewhat, much, very much”, The A criterion is met if the alternatives “much” or “very much” is chosen on item 1, 2 or 3, and 4. The three categories of PTSD symptoms (in total 17 items) assess re-experiencing (B-criterion), avoidance (C-criterion), and arousal symptoms (D-criterion). The response options for these three categories are “never/ not at all, rarely, sometimes, often” and to be accounted for as presence of a symptom, the alternatives “sometimes” or “often” are required. In accordance with the DSM-IV one of five B items, three of seven C items, and two of five C items are required to fulfil the criteria respectively. The duration criterion (E) is fulfilled if symptoms have been present for 1 month at least. The influence criterion (F) is met if the degree to which it influenced life was ≥ 6 with regard to at least one of the symptoms. The 17 symptom criteria are summed and higher score indicate higher prevalence of symptoms. The symptom scores have shown good internal reliability (*α* = .84) and split half reliability (.90). The difference between the two study arms as concerns the proportion of participants classified as fulfilling the criteria for PTSD at all assessment points will be reported. Means for the summed symptoms score (criteria B, C, and D) will be compared between the study arms. The TES has been adapted for this particular traumatic event (childbirth) where questions point directly at the childbirth [50]. The scale has been developed and evaluated in a Swedish context and thus is considered clinically relevant.

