## Discussion

Most women with negative experiences and PTSD FC have the ability to handle the psychological stress it may cause, but in previous studies a significant proportion of women have reported symptoms of posttraumatic stress, anxiety and depressive symptoms that need attention. However, little is known about how to treat psychological reactions in women with negative experiences from birth and it is unclear how symptoms are perceived and how they develop over time. For these reasons there is a growing recognition of the need to offer interventions for those suffering from mental illness related to reproductive events, and at the same time there is almost no published research on treatment for PTSD FC. To the best of our knowledge, only one RCT has examined the effect of iCBT for women with PTSD [42]. This study showed good outcome at the end of treatment for iCBT compared with a wait list condition. It is however uncertain whether trauma focused treatment for PTSD caused by events other than childbirth are suitable for those with negative experiences FC, and whether the long-term effects are beneficial for those with PTSD FC.

It is of particular importance to consider the recruitment process in clinical trials. In our study, the majority of the women in the participating study-centres rate their overall childbirth experience as part of the standard protocol at these centres. We contact all women with a low rating and believe that we address a majority of the women with a negative experience FC who have a potential need for psychological follow up. In our study we offer minimal therapeutic support which may affect compliance from the participants. We also know that people with trauma-related psychological problems often display avoidant behaviour and therefore some women may be reluctant and not motivated to accept offered psychological treatment.

Findings in this study will contribute knowledge and understanding of women with negative birth experiences and PTSD FC. The study will yield information about the psychological status in this group and a better understanding of potential cost-effective interventions that could improve women’s psychological health and quality of life. Hopefully this might reduce health care costs and promote positive bonding/relationship to the child and partner.

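### The two binary parts of the primary hypothesis are analysed only by chi-square and odds ratios; a baseline-adjusted repeated-measures logistic model would put them on the same footing as the continuous scores.

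*Protocol article*

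**What the plan says.** The primary hypothesis (Hypothesis, Primary) includes, beside lower symptom levels, a claim on PTSD classification: "a smaller proportion of participants classified as fulfilling the criteria for PTSD". It makes a parallel claim on the EPDS cut-off, again in favour of iCBT+TAU. Under Primary outcome measures, both proportions are to be reported at every assessment point.

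The Statistical analysis section then treats the two kinds of outcome differently:

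- Scores: "For the continuous data, a mixed model repeated measure (MMRM) will be used to evaluate treatment effects". The next sentence reads "All available data from all participants are used so this will be a suitable approach for intent-to-treat analysis".
- Proportions: chi-square "analysis and calculations of odds-ratios will be performed". No analysis set, missing-data rule or model is attached.
- Covariates: "We will also consider known risk factors for PTSD FC as covariates". This is tied to no outcome and no model.

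Per-protocol, completer and drop-out analyses are planned in addition. Procedure describes automatic reminders, a telephone call and paper questionnaires for women who do not respond. Table 3 shows that TES and EPDS are collected at baseline and at all six later assessments.

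In the TES description, the symptom rule is printed as "one of five B items, three of seven C items, and two of five C items are required to fulfil the criteria respectively".

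**The concern.** A mixed model can use a woman's baseline and other visits when one assessment is missing. A chi-square at a single visit cannot, and it has no place for a covariate. The intent-to-treat rationale is attached to the mixed model and nothing equivalent is said for the proportions. If the scores and the proportions disagree, the reader will not know whether the treatment acts differently on them or whether the two analyses used different women.

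Dropout is a reasonable worry here. Follow-up runs for four years, iCBT makes weekly demands that TAU does not, and the protocol plans to ask women randomised to iCBT who dropped out for their reasons. If the more severely affected women in the iCBT arm are the ones lost, the remaining iCBT women look better than the arm really is, and the error favours the new treatment.

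**Working it through.** **1. The plan's own figure.** Inputs from Sample size and power: w = 0.3, alpha 0.05, df = 1, power 0.8. N = (1.960 + 0.842)² / 0.3² = 87.2, rounded up to 88; the noncentral chi-square power at 88 is 0.804. The stated 88 reproduces and is not in dispute. It is a count of women analysed. If 130 are randomised (the t-test figure) and only women with data are tested, power for w = 0.3 is 0.86 at 20% loss and 0.82 at 30%. Bias matters more here than power.

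**2. When does a test on observed women go wrong?** Let p be the true proportion of cases, and r_c and r_n the response rates of cases and non-cases. The observed proportion is p·r_c / (p·r_c + (1 − p)·r_n), so the observed odds are the true odds times r_c / r_n. Hence

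observed OR = true OR × (r_c / r_n in iCBT) / (r_c / r_n in TAU).

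If the ratio is the same in both arms it cancels. With a true OR of 1, a TAU ratio of 1 and assumed iCBT response rates:

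- 0.6 / 0.7 gives OR 0.86
- 0.5 / 0.7 gives OR 0.71
- 0.5 / 0.8 gives OR 0.63
- 0.8 / 0.6 gives OR 1.33, so the direction can reverse

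Example with p = 0.30 and 0.5 / 0.7: 0.15 / (0.15 + 0.49) = 0.234 instead of 0.30.

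**3. Simulation with no true effect.** The outcome is a thresholded normal variable correlated 0.6 with baseline severity, and the chi-square uses observed women only. The 15.7% prevalence is the high-risk figure in the Background and N = 130 is from Sample size and power. The 30% prevalence, N = 260, the correlation, the loss rates and the slopes (log-odds of loss per SD of baseline severity) are assumptions.

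| Loss | Slope | Prevalence | Spurious difference (points) | Type I error |
|---|---|---|---|---|
| 15% TAU (random), 30% iCBT | 1.0, iCBT only | 15.7% | -3.9 | 8.4% (N = 130), 12.0% (N = 260) |
| as above | 1.0, iCBT only | 30% | -5.5 to -5.6 | 9.5%, 14.5% |
| as above | 0.5, iCBT only | 15.7% and 30% | -2.1 to -3.1 | 5.8% to 7.7% |
| 15% TAU, 30% iCBT | 1.0, both arms | 15.7% | -1.6 | 5.4%, 6.8% |
| 20% in both arms | alike in both arms | 15.7% and 30% | at most 0.1 in size | 4.8% to 5.2% |

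**4. The alternative.** Logistic regression on arm and baseline, standardised to all randomised women, had bias of at most 0.2 points and type I error of 3.7% to 5.2% when loss was severity-driven in iCBT only. It succeeds because loss there depends on observed baseline; it would not fully remove bias from loss that depends on the unseen outcome, as in step 2. With no dropout, adjustment raises power from 0.37 to 0.40 at 15.7% prevalence and from 0.53 to 0.60 at 30%.

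**5. The PTSD rule.** The TES text defines re-experiencing as B, avoidance as C and arousal as D, and speaks of 17 items. The printed counts are 5 + 7 + 5 = 17, but the last group of five carries the letter C, so D has no threshold as printed. Posttraumatic stress following childbirth, in the Background, lists B, C and D all as required.

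**The case against.** The strongest reply is that this is a condensed article. Missing-data handling for binary outcomes may be written in an analysis plan that is not shown, and silence on it is no fault. That stands. A reader might infer that the plan restricts the binary analysis to responders and is therefore not intent-to-treat. The documents do not say so: nothing rules out imputation, and an unadjusted comparison of randomised arms is valid with complete data. What remains is the method that is stated, which is weaker than the one chosen for the scores.

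A reader might also infer that the chi-square is valid only if loss is completely at random within each arm, or that a false benefit for iCBT is to be expected. Neither is supported. Under the null the test keeps its size when loss works alike in both arms, and the larger errors need strong severity-driven loss in iCBT alone. The Discussion's remark that "people with trauma-related psychological problems often display avoidant behaviour" concerns willingness to take up treatment. Questionnaires are chased separately, by reminders, telephone and post.

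The covariate sentence shows that adjustment was in mind, but it names no model and a chi-square cannot take covariates. The power gain from adjustment is modest, and chi-square does match the sample-size basis.

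Finally, a reader might take the printed PTSD rule to mean that arousal is never required. The item counts and the Background definition point to a slip in the letter. It is editorial and has nothing to do with dropout.

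**Conclusion.** The point holds as a worthwhile change of method, not as proof of bias. Two of the four components of the primary hypothesis are assigned an analysis that ignores baseline and other visits and, without imputation, excludes women with a missing assessment, while the other two get a model that does better on each count.

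Under assumed loss of 15% and 30%, the spurious difference runs from about -1.6 to -5.6 points and type I error from 5.4% to 14.5%. The values depend on prevalence, N, how strongly loss follows severity, and in which arm. With like dropout in both arms there is no material bias. The protocol states neither a dropout rate nor a mechanism, so these are illustrations of what the choice exposes the trial to.

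The criterion-letter slip is real, separate and minor. It still deserves correction, because the same classification defines a primary outcome and determines who is offered step 2.

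**What to change.** Make the main analysis of each binary primary outcome a repeated-measures logistic model, either mixed-effects or GEE after multiple imputation. Include arm, visit, arm by visit and the baseline value of the same scale, and include all randomised women. Report the marginal risk difference and odds ratio at each visit. Keep the chi-square as a descriptive complement. State the analysis set and the missing-data assumption for these outcomes beside those for the scores.

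The cost is a change of wording and slightly more analysis work. The baseline and follow-up TES and EPDS values are already collected, so no new data are needed.

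Separately, reconcile the printed TES symptom rule with the B, C and D definitions in the same section and in the Background, and check that the scoring code on the platform matches the reconciled text.
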